#### Sample size

We hypothesized that single- or multiple-umbilical cord cleansing with 4.0% chlorhexidine solution would result in a 20-30% reduction in neonatal mortality among enrolled infants, based on reductions observed in the previous Nepal trial. Sample size calculations were based on 20% Type II error (80% power), 5% Type I error, and10% loss to follow-up, and the presumed design effect (1.2) was estimated from mean cluster size and coefficient of variation from the previous Projahnmo activities. The expected neonatal mortality rate (NMR) in the dry cord care group was estimated at 36/1000, which accounted for a 30% reduction in NMR expected after implementing the basic package across all 133 clusters. As not all infants were expected to be met immediately at birth, sample size calculations were based on assuming that a proportion of NMR would occur prior to enrolment. Varying this proportion and the overall desired detectable reduction in mortality among enrolled infants enabled estimation of required sample sizes (Table 2). We ultimately assumed that 20% of neonatal deaths would occur prior to enrolment, requiring approximately 28,797 newborns (9,600 in each group) to detect a difference of 25% in mortality among enrolled infants. A power curve displaying the power to detect a range of differences under this fixed sample size is shown in Figure 3. At a rate of 12,500 births per year, we expected to fully enrol the required number within 2.3 years. Due to the size of the study area and the large number of clusters, the trial initiation was phased-in across the 133 clusters between June and December of 2007; the staggered implementation was balanced on treatment groups.

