#### Data Safety and Monitoring Board and Interim Analyses

An independent Data Safety Monitoring Board (DSMB) consisting of national and regional experts was established. Interim analyses were conducted after 31.3% (March 2008) and 69.8% (January 2009) of the expected sample size was recruited. These data were presented to the DSMB in both electronic reports and face-to-face meetings in Dhaka, Bangladesh. Stopping guidelines for efficacy were agreed upon by the DSMB members and the investigating team prior to the trial, using Lan-DeMets boundaries and nominal p-values for group sequential analyses estimated using O'Brien/Fleming spending function[17,18]. At each of the meetings, the DSMB recommended continuation of the project as originally planned.

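### The printed control mortality of 36/1000 does not give the 28,797 newborns or the rest of Table 2; the table corresponds to 38.5/1000, so text and table need reconciling

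*Protocol article*

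**What the plan says.** All inputs are in the protocol article, section Sample size.

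- Error rates and loss: "Sample size calculations were based on 20% Type II error (80% power), 5% Type I error, and10% loss to follow-up". Sidedness is not stated.
- Clustering: "the presumed design effect (1.2) was estimated from mean cluster size and coefficient of variation", with the coefficient of variation taken from the earlier project at the same site.
- Control rate: "The expected neonatal mortality rate (NMR) in the dry cord care group was estimated at 36/1000". The section explains that this figure already includes a 30% fall expected from the basic care package. The rate before that fall is not given.
- Deaths too early to be prevented: "We ultimately assumed that 20% of neonatal deaths would occur prior to enrolment".
- Result: "requiring approximately 28,797 newborns (9,600 in each group) to detect a difference of 25% in mortality among enrolled infants".

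Table 2 gives nine totals for the same calculation, crossing 10%, 20% and 30% of deaths before enrolment with reductions of 20%, 25% and 30%. The 28,797 is its central cell. The formula is not named.

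**The concern.** A reader who puts the printed inputs into the usual two-proportion formula does not get 28,797. The gap is not one mistyped cell: by the formula that fits the table, every cell is about 7% below what 36/1000 requires. Either the text or the whole table rests on another value.

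The control event rate is the main planning assumption in a mortality trial. If 36/1000 was the planning value, the 80% power claim is too favourable. If it was not, the article misreports the rate on which the trial was sized, and anyone reusing these inputs for a similar trial would start from the wrong figure.

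**Working it through.** **Inputs.** Among enrolled infants, control risk p1 = NMR × (1 − share of deaths before enrolment), and p2 = p1 × (1 − reduction). I take alpha 0.05 as two-sided (assumption), so z = 1.960, and z = 0.8416 for 80% power. Inflation for clustering and loss is 1.2/0.9 = 1.3333. With three arms the multiplier on n per arm is 3 × 1.2/0.9 = 4.

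**Formulas.** With d = p1 − p2 and p̄ the mean of p1 and p2:

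- Uncorrected: n0 = [1.960·√(2p̄(1−p̄)) + 0.8416·√(p1(1−p1) + p2(1−p2))]² / d²
- Continuity-corrected: n = (n0/4)·[1 + √(1 + 4/(n0·d))]²

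**Step 1: the printed 36/1000, central cell.** p1 = 0.036 × 0.8 = 0.0288; p2 = 0.0288 × 0.75 = 0.0216; d = 0.0072.

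- n0 = (1.960 × 0.22165 + 0.8416 × 0.22159)² / 0.0072² = 7,437.4. Total = 4 × 7,437.4 = 29,750, which is 3.3% above 28,797.
- n = (7,437.4/4) × [1 + √(1 + 4/53.55)]² = 7,712.7. Total = 4 × 7,712.7 = 30,851, which is 7.1% above.

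Neither gives 28,797.

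**Step 2: which formula lies behind Table 2?** Divide each cell by 3 × n per arm at 36/1000. Without the correction, the implied inflation changes with the size of the reduction: about 1.280, 1.291 and 1.301 for 20%, 25% and 30%. One inflation factor should not do that. With the correction it is nearly constant, 1.2442 to 1.2449, so the table was built with the correction. The small remaining drift rises with the share of deaths before enrolment, which suggests that the base rate is off.

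**Step 3: the plan's figure reproduced.** Scanning the control NMR from 30 to 42 per 1000 with the corrected formula, the implied inflation is most uniform at 38.5/1000. Its mean there is 1.33333, which is the stated 1.2/0.9. Central cell: p1 = 0.0385 × 0.8 = 0.0308; p2 = 0.0231; d = 0.0077; n0 = 6,941.9; n = 7,199.3; total 28,797.1.

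| Deaths before enrolment | Reduction | Table 2 | 38.5/1000, 1.2/0.9 | 36/1000, 1.2/0.9 |
|---|---|---|---|---|
| 10% | 20% | 40,643 | 40,643.4 | 43,554.5 |
| 10% | 25% | 25,511 | 25,511.4 | 27,336.8 |
| 10% | 30% | 17,367 | 17,367.0 | 18,608.4 |
| 20% | 20% | 45,883 | 45,883.4 | 49,158.3 |
| 20% | 25% | 28,797 | 28,797.1 | 30,850.6 |
| 20% | 30% | 19,602 | 19,601.6 | 20,998.1 |
| 30% | 20% | 52,620 | 52,620.5 | 56,363.3 |
| 30% | 25% | 33,022 | 33,021.5 | 35,368.4 |
| 30% | 30% | 22,474 | 22,474.5 | 24,070.6 |

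(Both computed columns are continuity-corrected.) At 38.5/1000 every cell agrees to about half an infant.

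**Step 4: power at 28,797.** Per arm 28,797/3 = 9,599; effective size 9,599 × 0.9/1.2 = 7,199.

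- 36/1000, uncorrected: z = (0.0072·√7,199 − 1.960 × 0.22165)/0.22159 = 0.796, power 78.7%.
- 36/1000, corrected: replace 7,199 by 7,199 × [1 − 1/(7,199 × 0.0072)]² = 6,924; z = 0.743, power 77.1%.
- 38.5/1000, corrected: power 80.0%.

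**The case against.** The text says the number is approximate and names no formula, so some slack is fair. Two uncorrected variants at 36/1000 come within 3% of the central cell: taking loss as × 1.1 gives 29,454 (+2.3%), and conditioning the control risk on survival to enrolment gives about 29,529 (+2.5%). But the × 1.1 variant misses all three cells for a 20% reduction by 3.1%, and no uncorrected formula removes the drift across columns. A table that matches another rate to the nearest infant in nine cells out of nine leaves little to approximation.

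A reader might infer from the implied 1.245 that clustering or loss was under-allowed, for instance a design effect of 1.12 with 10% loss (1.12/0.9 = 1.2444), or 1.2 with about 3.6% loss. The document does not support this. At 36/1000 with 1.12/0.9 the cells are missed by −7.8 to +14.2 infants in a systematic pattern, whereas 38.5/1000 with the stated 1.2/0.9 fits to rounding. The 1.245 arises only if 36/1000 is held fixed.

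What stands of the objection is that the size is modest, and that there may be no shortfall at all.

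**Conclusion.** The printed control rate and Table 2 do not agree. On the printed 36/1000 the required total is 29,750 uncorrected or 30,851 corrected, and 28,797 gives 78.7% or 77.1% power, a loss of 1.3 or 2.9 points against 80%. If 38.5/1000 was the planning rate, the size and the 80% follow exactly and only the text is wrong.

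It would go too far to say that the trial was underpowered: that holds only if 36/1000 was the planning value, and the table points the other way. Nor do the two interim looks explain the mismatch, since all nine cells are reproduced without any allowance for them.

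The conclusion rests on a two-sided 5% test and on the continuity correction, neither of which the article states; both are supported by the fit. That 38.5 equals 55 × 0.7, and so would suit the 30% basic-package reduction, is suggestive only: 55/1000 appears nowhere in the document, and 36/0.7 would be 51.4. The document alone cannot settle which rate was intended.

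**What to change.** State the control NMR actually used for Table 2, and that a two-sided test with continuity correction was applied. Then one of two corrections follows:

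- If 38.5/1000 was used, replace 36/1000 in the Sample size section. Table 2, the 28,797 and the 80% power stay.
- If 36/1000 is the planning rate, recompute Table 2 (the central cell becomes 30,851) and the power curve in Figure 3, and restate power at 28,797 as about 77% by the table's own method, or 79% uncorrected.

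The design effect of 1.2 and the 10% loss need no change. I could not check Figure 3; it should rest on the same rate as the table. The cost is one number in the text, or one table, one figure and a slightly lower stated power. Enrolment does not change.

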**Figure 3 F3:**
[figure not shown]
**Power to detect a range of differences in mortality risk between group**.

**Table 2 T2:** Total required number of newborns required for a range of detectable differences in mortality, by proportion of NMR occurring prior to enrolment

	**Detectable Difference in Mortality**		
	
**Proportion of neonatal mortality occurring prior to enrolment**	**20%**	**25%**	**30%**
**10%**	40643	25511	17367

**20%**	45883	**28797**	19602

**30%**	52620	33022	22474

#### Data Management and Analysis

CHWs collected data using maternal-level forms during their routine area monitoring and the two pregnancy visits, and infant-level forms during their follow-up visits to the newborns. The VHW-collected pictorial information on intervention visits in the first 7 days of life (date, time, visit status) was confirmed by CHWs through discussion with family members and then transferred to the infant-level forms maintained by the CHWs. All forms were checked for completeness daily by CHWs and at fortnightly meetings with supervisory staff, and then transferred to Dhaka for entry into a customized Microsoft SQL Server database. Entry programs included standard range and validation checks. Selected process-related data variables were entered at the field level to enable rapid feedback on essential implementation variables (e.g. enrolment, coverage and timing of home visits, etc.) to the field level supervisory staff.

For the final (and interim) analyses descriptive statistics on enrolment rates, timing of intervention delivery, frequency and coverage of home visits, receipt of components of the basic package, reported care practices, and health and demographic characteristics of newborn, mother, and households will be examined for balance across the groups. The primary impact analyses will follow an intent-to-treat approach among all enrolled infants, and will focus on comparing the mortality experience of newborns across the three cord care regimen groups. The mortality rate per 1000 live births will be estimated for all groups, and risk of death in each of the intervention groups (multiple and single cleansing) relative to the dry cord care group will be calculated. Standard errors will be adjusted for the clustered allocation using the generalized estimating equation approach[16], and 95% confidence intervals will be estimated. If necessary, adjusted models will be constructed to account for any imbalance between the groups.

Individual signs of cord infection and omphalitis under three sign-based algorithms (mild, moderate, severe) will be compared between groups using similar regression models with adjustment for both clustered design and multiple measures per baby. Individual visit level cord assessment data will be collapsed over the neonatal period with binary indicators created for each of the sign-based algorithms to estimate cumulative incidence of cord infection and risk of omphalitis relative to the comparison dry cord group.

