A large community-based trial[8] in rural southern Nepal conducted between 2002 and 2006 randomized babies within clusters to receive one of three cord care regimens: (1) 4.0% chlorhexidine cleansing for 7 of the first 10 days after birth or (2) soap and water cleansing for 7 of the first 10 days after birth, or (3) dry cord care. Mothers of all infants received educational messages about hygienic cord care (e.g., hand-washing, clean cutting, and avoidance of harmful topical applications). Depending on the severity of infection, omphalitis incidence was reduced by 32-75% among infants receiving chlorhexidine compared to those in the dry cord care group. Overall, mortality among enrolled infants was 24% lower in the chlorhexidine group compared to dry cord care. About two-thirds of the infants were reached within 24 hours of birth and evidence of a protective benefit of chlorhexidine cleansing among this subset was increased. Chlorhexidine cleansing reduced severe infection by 87% and mortality by 34% among those enrolled within 24 hours, while no difference between the groups was observed when cord cleansing was initiated after 24 hours[8].

An expert consultative meeting convened in Washington, DC shortly after completion of the Nepal trial concluded that, prior to any changes in policy, at least one replication trial in South Asia would be necessary to expand the evidence base for chlorhexidine cleansing of the cord[9]. Two specific questions were noted. First, would a similar beneficial effect of multiple cleansings of the cord through the first week of life be observed in a separate but similar population? Second, can a simpler regimen of cord cleansing only once and as soon as possible after birth, provide a similar protective benefit against omphalitis and mortality? Answering this second question is necessary as the intensive intervention (cleansing on 7 of first 10 days of life) followed in the Nepal efficacy trial might not be easily implemented in most programmatic settings, given associated logistical and financial barriers for outreach health workers. Furthermore, even if the intervention was delivered by caretakers themselves, compliance with the promoted instructions might be increased if the more simple recommendation of one-time cleansing as soon as possible after birth could be given. Moreover, a single application of antiseptic to the cord could more readily be incorporated into clean birth kits.

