## Discussion

Due to report in early 2010, the Projahnmo Chlorhexidine Study will provide an evaluation of the impact of multiple- or single cord cleansing with 4.0% chlorhexidine relative to the current WHO recommended dry cord care on neonatal mortality and omphalitis. The results from this trial will expand the evidence base for the use of topical chlorhexidine as a low-cost, simple-to-deliver intervention, and it's potential to reduce neonatal mortality and morbidity in low resource settings. Furthermore, it will provide new information on one-time cleansing of the umbilical cord and its potential effect relative to multiple cleansing. Since the chlorhexidine intervention was implemented in the context of a basic package of maternal and newborn care, this study will provide data on the impact of chlorhexidine cleansing which is additional to the effect of the basic package of care which is being scaled up in Bangladesh.

Rural Sylhet District of Bangladesh is an appropriate location for examining the impact of chlorhexidine interventions, with strong potential for generalizing results to the wider South Asian region. The rate of home births, overall neonatal mortality rates, and the proportion of deaths attributed to infection in this region are high and comparable to large parts of Bangladesh, India, Nepal and Pakistan. Access to care and care-seeking by households is low and identification of interventions that can improve survival and be delivered by community-based workers or caretakers in the household is urgently needed. The existing Projahnmo Project provided a highly capable and well-developed infrastructure for conducting a population-based community trial. Most importantly, Projahnmo represents a strong partnership that includes the Government of Bangladesh, local and international research institutes and NGOs. This broad-based partnership will increase the likelihood that if the intervention is found successful, it will be incorporated into national policy recommendations and scaled up within Bangladesh.

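### The article asks whether single cleansing protects about as well as multiple cleansing, but every effect measure it names, and the sample size, is against dry cord care

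*Protocol article*

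**What the plan says.** The Background lists two questions left open after the Nepal trial. The second is whether cleansing once, soon after birth, can "provide a similar protective benefit against omphalitis and mortality". The Discussion says the trial will supply "new information on one-time cleansing of the umbilical cord and its potential effect relative to multiple cleansing".

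Under Data Management and Analysis, the primary mortality analysis is first described in general terms, as a comparison over all three arms. The effect measure is then made specific: "risk of death in each of the intervention groups (multiple and single cleansing) relative to the dry cord care group will be calculated". Standard errors come from generalized estimating equations (GEE), with 95% confidence intervals. Cord signs and omphalitis are to be compared between groups with similar models, and the risk named there is again relative to the dry cord group.

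The Sample size section uses "20% Type II error (80% power), 5% Type I error, and10% loss to follow-up", a design effect of 1.2 and a 25% reduction among enrolled infants. It gives no difference, margin or power for single versus multiple cleansing.

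**The concern.** The second question concerns one active regimen relative to the other. The named estimates each compare one active regimen with control. Dividing the two risk ratios gives a point estimate of single versus multiple. The two published intervals do not give its uncertainty, because both estimates share the dry-care arm and their covariance would not be reported.

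The choice of regimen is a policy choice: the Background explains that the multi-day schedule may be hard to deliver in programmes. If no direct interval is given, a reader is likely to look at which regimen reached significance against dry care. That can make equally effective regimens look different. If both reach significance, it can make them look interchangeable when the data cannot show this.

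**Working it through.** **Inputs (Sample size section).**
- Dry-care mortality: "The expected neonatal mortality rate (NMR) in the dry cord care group was estimated at 36/1000".
- Deaths before enrolment: "We ultimately assumed that 20% of neonatal deaths would occur prior to enrolment". The control risk among enrolled infants is therefore 0.036 × 0.80 = 0.0288.
- A 25% reduction gives 0.0288 × 0.75 = 0.0216.
- Design effect 1.2, loss 10%, type I error 5%, power 80%. Two-sided testing is assumed, because the article does not state sidedness.
- Planned size 28,797, or 9,600 per arm.

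**1. Reproduce the plan's figure.** For two proportions with pooled variance under the null and p̄ = 0.0252:

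n = [1.96·√(2 × 0.0252 × 0.9748) + 0.8416·√(0.0288 × 0.9712 + 0.0216 × 0.9784)]² / 0.0072² ≈ 7,438 per arm.

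7,438 × 1.2 × 1.1 × 3 ≈ 29,454, which is 2.3% above 28,797. Dividing by 0.9 for loss, instead of multiplying by 1.1, gives 29,752 (3.3% above). The stated size is therefore that of one active arm against dry care at an unadjusted 5% level. Power at 9,600 per arm is 78.7%.

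**2. Effective size per arm.** 9,600 × 0.9 / 1.2 = 7,200.

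**3. Precision of the direct contrast when both arms truly have a 25% reduction.**
- SE(log RR) = √[2 × (1 − 0.0216) / (7,200 × 0.0216)] = √(1.9568 / 155.52) = 0.112.
- exp(1.96 × 0.112) ≈ 1.25, so the 95% interval around 1.0 is about 0.80 to 1.25.
- On the absolute scale the half-width is 1.96 × √(2 × 0.0216 × 0.9784 / 7,200) = 4.7 per 1000. The full 25% effect is 7.2 per 1000.

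**4. Why the two dry-care intervals do not substitute.**
- The variance of each log RR against dry care is 0.9784/155.52 + 0.9712/207.36 = 0.00629 + 0.00468 = 0.01097.
- Adding the two as if independent gives 0.02195, SE 0.148 and an interval of about 0.75 to 1.34.
- The correct variance removes the shared control term twice: 0.02195 − 2 × 0.00468 = 0.0126, SE 0.112, as in step 3.

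**5. What judging by significance against dry care would do.** Results are from 400,000 simulated trials with 7,200 effective infants per arm.

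| True reduction (multiple, single) | Both significant | Exactly one significant | Direct contrast significant |
|---|---|---|---|
| 25%, 25% | 67% | 23% | 5% |
| 30%, 20% | 57% | 37% | 22% |

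A bivariate normal calculation with correlation 0.5 gives 0.670 and 0.235 for the first row. In the second row, multiple alone is significant in 35% of trials.

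**6. Illustrative non-inferiority size** (margins are assumptions; one-sided 0.025, 80% power, 21.6 per 1000 in both arms).
- Margin of half the effect, 3.6 per 1000: n = (1.96 + 0.8416)² × 2 × 0.0216 × 0.9784 / 0.0036² ≈ 25,598. Multiplying by 1.2/0.9 gives about 34,100 per arm, against 9,600 planned.
- Margin of the whole effect, 7.2 per 1000: 6,400 × 1.2/0.9 ≈ 8,530 per arm, which the plan does reach.

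**The case against.** A reader might infer that the plan settles the second question by comparing two p-values, or that it rules out any contrast except the two against dry care. The article supports neither reading. It plans risk ratios with 95% intervals, and nominal p-values appear only for the interim stopping boundaries. Its general sentences about comparing all three arms, and about comparing omphalitis between groups, leave room for a direct contrast.

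It can also be argued that equivalence was never the objective. The similarity wording reports questions from an expert meeting. The last paragraph of the Background restates the second one as the potential efficacy of a single application, which single versus dry answers. The hypothesis and sample size fit that reading, no margin is claimed, and the Discussion's main sentence is about each regimen against dry care. A condensed article may also leave a secondary contrast to the full protocol or analysis plan, which is not shown.

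Much of this stands. The 23% describes a way of reading the results, not a rule in the plan, and no equivalence claim is made. What remains is that the article does specify its contrasts, and those do not match its similarity question or its promise of an effect relative to multiple cleansing. The efficacy wording withdraws neither.

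**Conclusion.** The point holds as a mismatch between a stated question and the effect measures named to answer it. The comparisons with dry care and the sample size for them are unaffected.

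On mortality, the trial can estimate single versus multiple only to within about 0.80 to 1.25, even if the observed ratio is exactly 1.0. It could exclude single cleansing losing the whole 25% effect. It is far too small to show that single cleansing keeps at least half of it.

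These figures assume two-sided 5%, the article's design effect of 1.2 and 10% loss, a control risk of 28.8 per 1000 among enrolled infants, and no allowance for the two interim looks. The article gives no expected omphalitis incidence, so no width is computed for that outcome.

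**What to change.** In Data Management and Analysis, name a single-versus-multiple risk ratio with 95% confidence interval from the same GEE model, for mortality and for omphalitis, and label it as estimation. State that any conclusion about the regimens relative to each other rests on that interval and not on which regimen is significant against dry care. Add that, at the planned size, the mortality interval would be about 0.80 to 1.25 around 1.0, so similarity within about 25% cannot be shown.

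Alternatively, limit the second question to efficacy against dry cord care, as the end of the Background already does, and align the Discussion sentence with it.

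Either change should be made before results by arm are analysed. The first costs one extra contrast from a model already planned; the second is wording alone. Neither needs new data. The downside is a less favourable statement of what the trial can say about similarity.
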